### Management of Dropout Cases

All patients who provide informed consent and meet the eligibility criteria for enrollment in this randomized controlled trial, irrespective of the timing or reasons for their withdrawal later, will be categorized as dropouts if they are lost to follow-up. However, patients who discontinued the treatment regimen because of complete symptom remission will not be considered dropouts. The investigators will comprehensively document the reasons for each dropout in the case report form. Real-world circumstances, including adverse events (AEs), will be accounted for during the statistical analysis. In addition, we will carefully record and preserve the data about all enrolled patients who will receive the assigned investigational medications, regardless of their withdrawal status, for observation purposes and to be used as a data archive and for the intention-to-treat analysis.

### Interventions

All patients will be provided with detailed information about the study. Once informed consent is obtained and baseline assessments are completed, eligible patients will be randomly allocated to the intervention or placebo group. Notably, the investigational drug in this study was Chinese medicine, so patients were required not to take other Chinese medicine or Chinese patent medicine throughout the study. Both groups will receive standard treatments. In addition to the standard treatment, the intervention group will receive DaXianXiong decoction (Figure 2). The constituent botanical drugs of the DaXianXiong decoction are listed in Table 1. DaXianXiong decoction includes three herbs, namely, 30 g of Rhei Radix et Rhizoma (Shengdahuang), 30 g of Natrii Sulfas (Mangxiao), and 3 g of Kansui Radix (Gansui). The dosage of each herb was determined based on the guidelines outlined in *The Chinese Pharmacopoeia*, 2020 edition [16].

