**Figure 2 figure2:**
[figure not shown]
Components of DaXianXiong decoction.

**Table 1 table1:** Components of DaXianXiong decoction.

Drug name	Part this formula uses	Location of manufacture	Dose (g)	Use	Medicine form, dosage, frequency	Registration status (yes/no)	Quality control report (yes/no)	Storage condition
Da Huang (Rhei Radix et Rhizoma)	Roots	Sichuan Neautus Co, Ltd, Sichuan, China	7.5	Nasal feeding or oral administration	Powder, dissolved in 50 mL of warm water, every 6 h, lasts 48 h	Yes	Yes	Powder: stored in the pharmacy department; 18-20 °C and 45%-75% humidity Decoction: kept in the ward; 26-28 °C and 50%-60% humidity
Mang Xiao (Natrii Sulfas)	Mineral	Sichuan Neautus Co, Ltd, Sichuan, China	7.5	Nasal feeding or oral administration	Powder, dissolved in 50 mL of warm water, every 6 h, lasts 48 h	Yes	Yes	Powder: stored in the pharmacy department; 18-20 °C and 45%-75% humidity Decoction: kept in the ward; 26-28 °C and 50%-60% humidity
Gan Sui (Kansui Radix)	Roots	Sichuan Neautus Co, Ltd, Sichuan, China	0.5	Nasal feeding or oral administration	Powder, dissolved in 50 mL of warm water, every 6 h, lasts 48 h	Yes	Yes	Powder: stored in the pharmacy department; 18-20 °C and 45%-75% humidity Decoction: kept in the ward; 26-28 °C and 50%-60% humidity

The Department of Pharmacy of the Chongqing Traditional Chinese Medicine Hospital will perform the following processing steps on DaXianXiong decoction: water extraction, separation, concentration, drying, and granulation. Each sachet will contain 10.5 g of powdered decoction. The production and processing procedures will be conducted as per the guidelines specified in *The Chinese Pharmacopoeia*. The powder will be processed and filled in standardized clean production workshops. The treatment method will involve nasal feeding or oral administration of DaXianXiong decoction four times a day, once every 6 hours, and dissolved in 50 mL of warm boiled water. The course of the treatment will be 48 hours.

We will design placebos similar to the intervention drugs in terms of shape, color, smell, and solubility so that patients have a similar sensory experience. Placebos have no efficacy or side effects. They will also be produced by the Department of Pharmacy of the Chongqing Traditional Chinese Medicine Hospital.

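### The Kansui Radix amount in the Interventions text cannot be reconciled with Table 1: 3 g against 2 g a day when the other two components agree

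*Protocol article*

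**What the plan says.** Three places in the protocol article, all under Methods, Interventions, give figures for the product.

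- **Running text.** The formula is "30 g of Rhei Radix et Rhizoma (Shengdahuang), 30 g of Natrii Sulfas (Mangxiao), and 3 g of Kansui Radix (Gansui"). No period is attached: the text does not say whether this is per day, per course or per batch. It adds that each herb's dosage follows the 2020 Chinese pharmacopoeia.
- **Table 1.** The dose column reads "Da Huang (Rhei Radix et Rhizoma) Roots Sichuan Neautus Co, Ltd, Sichuan, China 7.5", "Mang Xiao (Natrii Sulfas) Mineral Sichuan Neautus Co, Ltd, Sichuan, China 7.5" and "Gan Sui (Kansui Radix) Roots Sichuan Neautus Co, Ltd, Sichuan, China 0.5" (all in g). Each row gives the frequency as 6-hourly and the duration as 48 hours.
- **Text below Table 1.** The hospital pharmacy extracts, dries and granulates the product. "Each sachet will contain 10.5 g of powdered decoction". It is given "four times a day, once every 6 hours, and dissolved in 50 mL of warm boiled water", for 48 hours.

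The article gives neither the number of sachets per administration nor a ratio of crude herb to finished powder.

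**The concern.** The running text and Table 1 list amounts of the same three named components, so one list should be a fixed multiple of the other. It is not. Two components scale by one factor and Kansui by another.

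The decoction is the only experimental treatment, and the trial sets out to judge both its efficacy and its safety. If the Kansui content is uncertain by half, any benefit or adverse event cannot be tied to a known exposure to that component, and another group could not reproduce the regimen. The Discussion presents the study as a possible step towards larger multicenter trials, which would need a single composition. A reader also cannot tell which of the two Kansui amounts the pharmacopoeia statement is meant to support.

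**Working it through.** **Inputs.** Running text: 30 / 30 / 3 g (Rhei / Natrii Sulfas / Kansui). Table 1: 7.5 / 7.5 / 0.5 g. Sachet: 10.5 g. Frequency: 4 a day. Duration: 48 h, so 4 × 2 = 8 administrations.

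**Step 1: ratios, which need no assumption about period.**
- Text: 30 : 30 : 3 = 10 : 10 : 1.
- Table 1: 7.5 : 7.5 : 0.5 = 15 : 15 : 1.

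The ratios differ, so no common multiplier turns one list into the other.

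**Step 2: divisor from text to Table 1, component by component.**
- Rhei: 30 / 7.5 = 4.
- Natrii Sulfas: 30 / 7.5 = 4.
- Kansui: 3 / 0.5 = 6.

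The divisor of 4 equals the stated number of doses a day. This makes it natural to read the text as a daily amount and Table 1 as the amount per administration.

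**Step 3: size of the conflict on that reading.**

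| | Table 1 | Text, read as daily |
|---|---|---|
| Rhei, per day | 4 × 7.5 = 30 g | 30 g |
| Natrii Sulfas, per day | 4 × 7.5 = 30 g | 30 g |
| Kansui, per day | 4 × 0.5 = 2 g | 3 g |
| Kansui, per dose | 0.5 g | 3 / 4 = 0.75 g |
| Kansui, over 48 h | 8 × 0.5 = 4 g | 2 × 3 = 6 g |

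The text figure is 3 / 2 = 1.5 times the Table 1 figure. Put the other way, Table 1 is one third below the text. Rounding does not explain a move from 0.75 to 0.5.

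**Step 4: the sachet, as a query.**
- Sum of Table 1: 7.5 + 7.5 + 0.5 = 15.5 g.
- Quarter of the text formula: 63 / 4 = 15.75 g.
- Sachet: 10.5 g, equal to neither.
- Sixth of the text formula: 63 / 6 = 10.5 g, made up of 5 / 5 / 0.5 g.

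A divisor of 6 therefore fits the sachet and the Kansui row but not the two 7.5 g rows. A divisor of 4 fits the two 7.5 g rows but neither Kansui nor the sachet. This pattern would arise if two divisors had been mixed, but that is inference; the article does not say so.

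**The case against.** The strongest reply is that most of the regimen is consistent. For two of the three components, Table 1 multiplied by four gives exactly the amount in the text. The interval, the 50 mL volume and the 48-hour duration agree between Table 1 and the text below it. This stands, and it confines the established conflict to one component. It does not remove that conflict.

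The second reply concerns the sachet. The powder is made by extraction and drying, so its weight need not equal the weight of the starting herbs, and the article does not say that one sachet is one dose. The preparation entry is the same in all three rows of Table 1 and can be read as describing the finished product. This also stands: a reader might infer from 15.5 g against 10.5 g that the dose mass is contradicted, but the document does not establish it. Processing loss is not a ready answer for Kansui, however. If Table 1 listed extract weights, two components falling at exactly a quarter of the formula would be hard to explain.

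Third, a reader might infer that ward staff following different sections would give different amounts. The article does not support this. The pharmacy fills the sachets, and under Blinding each patient receives a package with medication numbers and labels. The open question is what went into the sachets and how it is reported.

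Finally, an article may leave pharmacy detail to the full protocol. That is so, and a missing extraction ratio is no finding in itself. The point here is that two figures which are stated do not agree.

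**Conclusion.** The point holds for Kansui Radix. The ratios 10:10:1 and 15:15:1 are incompatible whatever period is assumed, and this needs nothing beyond the printed figures. The size (2 against 3 g a day, 0.5 against 0.75 g per dose, 4 against 6 g over 48 hours) rests on two readings: that the text gives a daily amount and that Table 1 gives the amount per administration. Both are supported by the exact match of the other two components at four doses a day.

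Two broader conclusions are not supported. One is that the whole tested dose is undefined: 30 g a day is consistent for Rhei and for Natrii Sulfas. The other is that all three components conflict. That follows only if 30 / 30 / 3 g is taken as the total for the 48-hour course, when Table 1 would give 60 / 60 / 4 g, and nothing in the article points to that reading. The sachet weight remains a query.

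The correction should still be made before results are reported, because the composition of the sole experimental product underlies every efficacy and safety statement. No view is taken on which Kansui amount is right.

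**What to change.** - Reconcile the Interventions text, Table 1 and the sachet weight against the pharmacy batch records, and correct whichever passage is found to be in error.
- State the period to which 30 / 30 / 3 g applies, and how the 10.5 g sachet relates to one administration.
- Process the correction as the Modification of the Protocol section requires, including the ethics committee.
- In the results paper, report the amount of each component that patients actually received.

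The cost is a check of existing records, a corrected passage or table, and a notification. The Results section says the data have been collected and are being analyzed; no new data are needed, and neither the sample size nor the analysis changes.

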**Figure 2 figure2:**
[figure not shown]
Components of DaXianXiong decoction.

**Table 1 table1:** Components of DaXianXiong decoction.

Drug name	Part this formula uses	Location of manufacture	Dose (g)	Use	Medicine form, dosage, frequency	Registration status (yes/no)	Quality control report (yes/no)	Storage condition
Da Huang (Rhei Radix et Rhizoma)	Roots	Sichuan Neautus Co, Ltd, Sichuan, China	7.5	Nasal feeding or oral administration	Powder, dissolved in 50 mL of warm water, every 6 h, lasts 48 h	Yes	Yes	Powder: stored in the pharmacy department; 18-20 °C and 45%-75% humidity Decoction: kept in the ward; 26-28 °C and 50%-60% humidity
Mang Xiao (Natrii Sulfas)	Mineral	Sichuan Neautus Co, Ltd, Sichuan, China	7.5	Nasal feeding or oral administration	Powder, dissolved in 50 mL of warm water, every 6 h, lasts 48 h	Yes	Yes	Powder: stored in the pharmacy department; 18-20 °C and 45%-75% humidity Decoction: kept in the ward; 26-28 °C and 50%-60% humidity
Gan Sui (Kansui Radix)	Roots	Sichuan Neautus Co, Ltd, Sichuan, China	0.5	Nasal feeding or oral administration	Powder, dissolved in 50 mL of warm water, every 6 h, lasts 48 h	Yes	Yes	Powder: stored in the pharmacy department; 18-20 °C and 45%-75% humidity Decoction: kept in the ward; 26-28 °C and 50%-60% humidity

The Department of Pharmacy of the Chongqing Traditional Chinese Medicine Hospital will perform the following processing steps on DaXianXiong decoction: water extraction, separation, concentration, drying, and granulation. Each sachet will contain 10.5 g of powdered decoction. The production and processing procedures will be conducted as per the guidelines specified in *The Chinese Pharmacopoeia*. The powder will be processed and filled in standardized clean production workshops. The treatment method will involve nasal feeding or oral administration of DaXianXiong decoction four times a day, once every 6 hours, and dissolved in 50 mL of warm boiled water. The course of the treatment will be 48 hours.

We will design placebos similar to the intervention drugs in terms of shape, color, smell, and solubility so that patients have a similar sensory experience. Placebos have no efficacy or side effects. They will also be produced by the Department of Pharmacy of the Chongqing Traditional Chinese Medicine Hospital.

In the event of a serious AE or allergic reaction caused by the research medication, the principal investigator will open the emergency envelope and discontinue the trial for that patient. Details of the event and unblinding will be recorded in the case report form, and the patient will receive appropriate treatment. The relevant departments and ethics committees will be promptly notified within 24 hours.

### Randomization

Randomization will be conducted by an independent statistician using SPSS Statistics 26.0 (IBM Corp) software. A predetermined random number table will be generated, and 60 patients will be randomly assigned to either the intervention group or the standard-of-care group in a 1:1 ratio. To ensure accuracy and reliability, a random distribution table will be created in triplicate, with copies provided to the project leader, pharmacist, and statistician. The statistician, who remains blind to the trial and is not involved in patient recruitment, will generate the allocation sequence and securely store the master randomization list. Randomization will be implemented using a sealed envelope method to maintain allocation concealment. Each patient will receive a unique study identification number upon enrollment. The randomization table will be used to sequentially assign these numbers to either the intervention or control group. Each assignment will be enclosed in an opaque, sequentially numbered, and sealed envelope. After obtaining informed consent, the recruiter will open the envelope corresponding to the patient’s study ID and determine the group assignment.

### Outcome Measures

The outcome measures will be determined at various time points throughout the study, including baseline (T0, before treatment), 24 hours after the final treatment (T1, end point 1), 3 days after the final treatment (T2, end point 2), 7 days after the final treatment (T3, end point 3), and 28 days after the final treatment (T4, final end point). The data collection and assessment schedule are listed in Table 2.

**Table 2 table2:** The data collection and assessment schedule.

Assessments		Study period				Follow-up		
		Enrollment and allocation (T0)	Intervention (48 hours)	Primary end point (T1)	T2		T3	T4

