## Introduction

Acute pancreatitis (AP) is a common yet potentially fatal inflammatory disorder of the pancreas, characterized by severe abdominal pain, multi-organ dysfunction, and pancreatic necrosis. The global incidence of AP is approximately 30-40 cases per 100,000 people, with over 2000 fatalities annually [1]. Severe AP (SAP), which involves persistent organ failure lasting ≥48 hours, is the most life-threatening form of AP, with a mortality rate of 20%-40% despite significant advancements in treatment [2-4]. Approximately 20% of patients with AP progress to SAP, which is associated with severe complications such as organ failure, infections, and increased health care costs [1,5].

The pathophysiology of AP is characterized by premature activation of trypsin within the pancreatic acinar cells, triggering pancreatic autodigestion and leading to a systemic inflammatory response. This response results in systemic inflammatory response syndrome, which can progress to multi-organ dysfunction syndrome [6,7]. Although the treatment of AP is mainly supportive, including fluid resuscitation and organ support, there remains a lack of consensus on the optimal management protocols for fluid therapy [8,9], and strategies to promote gastrointestinal recovery remain limited [10].

In addition to conventional Western treatments, Chinese herbal medicines have gained attention for their potential in managing AP. Chinese herbal medicines are known for their ability to target multiple biological pathways involved in inflammation, immune response, and organ protection, offering a broader approach compared to single-target Western therapies [11,12]. DaXianXiong decoction, a traditional herbal formula used in China for over 30 years, has been reported to improve gastrointestinal symptoms and modulate inflammation. However, its clinical efficacy in preventing the progression of AP to SAP has not been conclusively demonstrated due to the lack of robust randomized controlled trials [12-14].

In light of these challenges, there is an urgent need for high-quality studies to evaluate the efficacy and safety of DaXianXiong decoction in the treatment of AP. This study aims to assess the potential of DaXianXiong decoction in preventing the progression of AP to SAP, reducing inflammatory markers, improving gastrointestinal function, and assessing safety and complications.

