**Intervention**								
	Intervention group		✓					
	Placebo group		✓					
**Assessment**s								
	Incidence of SAP^a^			✓	✓		✓	✓
	Modified Marshall score	✓		✓	✓		✓	✓
	Modified CTSI^b^	✓		✓	✓		✓	✓
	APACHE II^c^ score	✓		✓	✓		✓	✓
	C-reactive protein	✓		✓	✓		✓	✓
	IL^d^-1	✓		✓	✓		✓	✓
	IL-4	✓		✓	✓		✓	✓
	IL-6	✓		✓	✓		✓	✓
	IL-8	✓		✓	✓		✓	✓
	IL-10	✓		✓	✓		✓	✓
	TNF^e^-α	✓		✓	✓		✓	✓
	Safety outcomes	✓		✓				
	Hospitalization							✓
	Survival							✓

^a^SAP: severe acute pancreatitis.

^b^CTSI: computed tomography severity index.

^c^APACHE II: Acute Physiology and Chronic Health Evaluation II.

^d^IL: interleukin.

^e^TNF: tumor necrosis factor.

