### Primary Outcomes

The primary outcome of this study is the incidence of SAP, which will be calculated using the following formula:

SAP incidence (%) = (number of SAP cases/total number of patients) × 100%

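### The primary time point is not fixed consistently, and the one visit labelled primary (T1, in Table 2) is too early for an outcome that needs 48 hours of organ failure

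*Protocol article*

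**What the plan says.** All references are to the protocol article.

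- **Primary Outcomes:** "The primary outcome of this study is the incidence of SAP". It is a proportion of patients, with no assessment time attached.
- **Introduction:** the only definition of SAP given is "Severe AP (SAP), which involves persistent organ failure lasting ≥48 hours".
- **Interventions (text after Table 1):** doses are given "four times a day, once every 6 hours". "The course of the treatment will be 48 hours".
- **Outcome Measures, text:** the visits include "24 hours after the final treatment (T1, end point 1") and "28 days after the final treatment (T4, final end point"). Neither is called primary.
- **Outcome Measures, Table 2:** the T1 column is headed "Primary end point (T1"). The SAP incidence row is ticked at T1, T2, T3 and T4.

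The Table 2 column heading is the only place where the word primary is tied to a time.

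**The concern.** The stated aim is to prevent progression from acute pancreatitis to SAP. An outcome that needs 48 hours of organ failure cannot be complete at a visit unless the failure began at least 48 hours earlier. T1 comes only 24 hours after treatment ends, and treatment itself lasts 48 hours. A T1 reading therefore reaches back only to the first half of the course.

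If T1 is used, failure that begins at hour 30 and lasts a week is classed as no SAP in the primary result, in either arm. Failure already present at the first dose counts if it persists, although treatment cannot have prevented its onset. The primary comparison would then lean towards cases the decoction had little chance to prevent and would leave out later cases, so any true difference would tend to be diluted.

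Asking the sponsor only to name one time point would not be enough, because naming T1 would leave this mismatch in place.

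**Working it through.** The article gives no figure for the onset window, so there is none to reproduce. The window follows from its schedule.

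**Inputs**
- Duration of organ failure needed for SAP: 48 h (Introduction).
- Dosing: every 6 h over 48 h (Interventions), so 8 doses at hours 0, 6, ..., 42.
- Visits: 24 h, 3 days (72 h), 7 days (168 h) and 28 days (672 h) after the final treatment (Outcome Measures).
- Final treatment: hour 42 if it means the eighth dose, hour 48 if it means the end of the course. Both are carried through.

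**Latest onset that can qualify at a visit** = final treatment + visit offset − 48 h. For T1: 42 + 24 − 48 = 18 h, or 48 + 24 − 48 = 24 h.

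| Visit | Hours after first dose | Latest qualifying onset (h after first dose) |
|---|---|---|
| T1 | 66–72 | 18–24 |
| T2 | 114–120 | 66–72 |
| T3 | 210–216 | 162–168 |
| T4 | 714–720 | 666–672 |

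By hour 18, four of the eight doses have been given (hours 0, 6, 12, 18). By hour 24, five have. The window has no lower limit at the first dose, since failure present at entry also qualifies if it persists.

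**Share of new-onset cases that can count at T1.** The article gives no onset distribution, so these patterns are assumptions:
- Uniform over 7 days: 18/168 = 11% to 24/168 = 14%.
- Exponential, median 48 h: 1 − 2^(−18/48) = 23% to 1 − 2^(−24/48) = 29%.
- Exponential, median 24 h: 1 − 2^(−18/24) = 41% to 1 − 2^(−24/24) = 50%.

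**Allowing for failure at entry.** The eligibility criteria do not exclude organ failure attributable to the pancreatitis itself at entry. If half of all SAP cases had it at entry (an assumption), the share of all SAP cases counted at T1 would be 0.5 + 0.5 × 0.23 = 61% with a 48 h median and the earlier cut-off, and 0.5 + 0.5 × 0.50 = 75% with a 24 h median and the later one.

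**Scale in cases.** The Introduction's figure of about 20% progressing to SAP gives 0.20 × 60 = 12 cases. If all 12 were new onset, 11% to 50% is roughly 1 to 6 of them.

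**The case against.** The strongest objection is that the premise rests on one column heading. That heading covers every assessment in the table, not SAP alone. The Primary Outcomes section has no time, the text numbers T1 merely as the first end point and T4 as the last, and no sentence says SAP will be tested at T1 only. Counting SAP cases over the whole follow-up fits the Primary Outcomes formula at least as well. This stands, and it makes the point conditional on the Table 2 label governing. It does not remove it, because no other text says which time is primary.

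A reader might infer that the trial misses later progression to SAP. The article does not support that: SAP and the modified Marshall score are both scheduled at T2, T3 and T4, so later cases are recorded. They drop out only of a primary analysis taken at T1.

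A reader might also infer that a T1 result could not answer the trial's question at all. That is too strong. Patients enter within 24 hours of illness onset, four or five doses come before the cut-off, and a difference at T1 would be evidence on early SAP.

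The size of the loss is also uncertain. An exponential onset with a 12 h median, no better supported than the patterns above, would let 65% to 75% of new-onset cases count: 1 − 2^(−18/12) to 1 − 2^(−24/12). No power loss is claimed here, because it would rest on these assumed patterns and on treating all of the 20% as new onset. Power is low in any case: 30 per arm gives about 19% for 20% against 10% with every case counted. That is a separate sample-size matter, which a later time point does not cure.

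**Conclusion.** The concern holds in conditional form. The article does not fix the primary time point consistently, and the one label that names a time points to a visit too early for its own definition of SAP. If that label is followed, only organ failure present at entry or beginning by hour 18 to 24 can enter the primary result, and later SAP is recorded but excluded.

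The 18 to 24 hour window follows from the article alone. The share lost does not. About 11% to 50% of new-onset cases would count under the three patterns tabulated, more if onset is earlier still, and a larger share of all SAP cases if some patients have organ failure at entry.

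This should be corrected before the comparison is made. It is a defect of wording and timing that scheduled data can repair, not one that invalidates the trial.

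**What to change.** 1. Remove the primary label from the T1 column of Table 2.
2. In Primary Outcomes, define the outcome as cumulative SAP from randomisation to one named visit that is already scheduled. T3 admits onset to about hour 162 to 168. T4, which the text already calls the final end point, admits onset to about hour 666 to 672. Either resolves the conflict.
3. Report SAP by T1 as descriptive only.
4. Make the Outcome Measures text, Primary Outcomes and Table 2 agree.
5. The Results section says data have been collected and are being analysed, so date and document the change before any unblinded comparison. If a comparison has already been seen, say so.

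The cost is wording, since no new visits or measurements are needed. The downside is slightly more missing data at the later visit than at T1.
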